## Abstract

**Background:**

Chronic back pain is a major public health problem and the primary reason patients seek acupuncture treatment. Therefore, an objective assessment of acupuncture efficacy is critical for making informed decisions about its appropriate role for patients with this common condition. This study addresses methodological shortcomings that have plagued previous studies evaluating acupuncture for chronic low back pain.

**Methods and Design:**

A total of 640 participants (160 in each of four arms) between the ages of 18 and 70 years of age who have low back pain lasting at least 3 months will be recruited from integrated health care delivery systems in Seattle and Oakland. They will be randomized to one of two forms of Traditional Chinese Medical (TCM) acupuncture needling (individualized or standardized), a "control" group (simulated acupuncture), or to continued usual medical care. Ten treatments will be provided over 7 weeks. Study participants and the "Diagnostician" acupuncturists who evaluate participants and propose individualized treatments will be masked to the acupuncture treatment actually assigned each participant. The "Therapist" acupuncturists providing the treatments will not be masked but will have limited verbal interaction with participants. The primary outcomes, standard measures of dysfunction and bothersomeness of low back pain, will be assessed at baseline, and after 8, 26, and 52 weeks by telephone interviewers masked to treatment assignment. General health status, satisfaction with back care, days of back-related disability, and use and costs of healthcare services for back pain will also be measured. The primary analysis comparing outcomes by randomized treatment assignment will be analysis of covariance adjusted for baseline value. For both primary outcome measures, this trial will have 99% power to detect the presence of a minimal clinically significant difference among all four treatment groups and over 80% power for most pairwise comparisons. Secondary analyses will compare the proportions of participants in each group that improve by a clinically meaningful amount.

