## Statistical issues

### Sample size and the detectable difference

The sample size was selected to have adequate power to detect a clinically significant difference of 2.0 points between groups on the Roland Disability scale. Our target sample size of 640 randomized individuals (160 per group) was computed using assumptions described below. Assuming 10% loss to follow-up for each group, there will be outcome data for 144 participants per group. The power of the overall analysis depends on how the four means are distributed. We used the pilot data to estimate the distribution of the means for the four groups and then computed an effect size that was used in the omnibus power calculation.

In the proposed analysis we will first determine if there is an overall difference among the four treatment groups using a two-sided significance level of 0.05. With 144 per group, this omnibus F-test will have 99% power for detecting a statistically significant difference among the four treatment means given the effect size obtained in the pilot study. If this omnibus test is statistically significant, we will compare specified pairs of means as indicated in the proposal. Because this will involve multiple post-hoc comparisons, we will use the Tukey-Kramer multiple comparisons procedure [36] to allow for all possible pairwise comparisons holding the overall α = 0.05. We will not consider a pairwise difference between the means to be statistically significant unless the t-value exceeds 2.61, instead of the usual 1.96.

Both primary outcomes (Roland Disability Questionnaire and bothersomeness of low back pain) are tested at the 0.05 level because they address separate scientific questions. The analyses of covariance of the 8-week pilot data provided estimates of the standard deviations of the primary outcome measures adjusted for pre-randomization baseline values: Roland SD = 4.71 and Bothersomeness SD = 2.73. Using these assumptions, the power to detect a pairwise difference of 2.0 Roland units is 84%, adjusted for multiple comparisons. For the bothersomeness outcome, for which a difference of 1.5 points is considered minimally clinically significant, we will have 98% power to detect a difference of this magnitude. Thus, if our assumptions are correct, 160 participants per group will provide adequate power to detect the smallest clinically meaningful differences on both of our primary outcome measures even after adjustment for multiple pairwise comparisons.

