In our secondary analyses, we will compare the proportions of participants in each treatment group who experience clinically significant improvement on our primary outcome measures.

We plan to conduct subgroup analyses of gender, study site, and race/ethnicity that will include an overall comparison of the four groups followed by specific pairwise comparisons. Power for some of these comparisons will be limited. While we will test a site by treatment interaction to determine if the treatment effects differ across the two sites, this test will only be sensitive to very pronounced effect modification by site.

In summary, we have high power to find an overall difference among the four groups even in some of the planned subset analyses. Although powered to detect clinically significant difference on the Roland Disability scale, the resultant sample size will provide ample power for our other primary outcome, bothersomeness of back pain, even in pairwise comparisons adjusted for multiple comparisons. Because our estimates are conservative, we are very likely to have adequate power even if the assumptions on which our power estimates are based prove incorrect. In addition, the proposed sample sizes will permit us to explore whether the findings apply equally to women and men and to different racial groups.

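### The abstract attaches the 99% omnibus power to the smallest important difference, but the methods attach it to the pilot effect size; for a 2.0-point Roland range the design gives about 87% to 99.5%

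*Protocol article*

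**What the plan says.** The abstract (Methods and Design) states for both primary outcomes that "this trial will have 99% power to detect the presence of a minimal clinically significant difference among all four treatment groups", and adds that most pairwise comparisons have more than 80% power.

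The section Sample size and the detectable difference describes the omnibus F-test, run "using a two-sided significance level of 0.05", as having "99% power for detecting a statistically significant difference among the four treatment means given the effect size obtained in the pilot study". It notes that omnibus power depends on the distribution of the four means and that the pilot supplied that distribution. It reports neither the means nor the effect size. The smallest important differences appear there only with the pairwise tests: 84% power for 2.0 Roland points and 98% for 1.5 bothersomeness points, using a critical t of 2.61. Pairwise tests follow only if the omnibus test is significant.

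The summary that closes the section says: "Because our estimates are conservative, we are very likely to have adequate power", and extends this to the case where the assumptions turn out wrong.

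**The concern.** The two places give the same 99% to two different alternatives. Power at the effect a pilot happened to show is not power at the smallest effect worth finding, and the abstract drops the condition on the pattern of means that the methods state.

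This matters most for Roland, the outcome the trial was sized on. The omnibus test is the gate to every pairwise comparison. Someone who relies on the abstract would give an important Roland difference only a 1% chance of being missed at that gate, and could read a null omnibus result as near proof that no such difference exists. The closing assurance about conservative estimates reinforces that reading without giving a margin.

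**Working it through.** **Inputs**, all from Sample size and the detectable difference: 160 randomised per arm; 10% loss, so "there will be outcome data for 144 participants per group" (160 × 0.90 = 144); each primary outcome tested at 0.05; baseline-adjusted pilot SDs of 4.71 (Roland) and 2.73 (bothersomeness); smallest important differences of 2.0 and 1.5; pairwise critical value 2.61.

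**The plan's pairwise figures.** Power ≈ Φ(δ / (SD × √(2/n)) − 2.61).
- Roland: 2.0 / (4.71 × √(2/144)) = 3.603; Φ(0.993) = 84.0%. Stated: 84%.
- Bothersomeness: 1.5 / (2.73 × √(2/144)) = 4.662; Φ(2.052) = 98.0%. Stated: 98%.

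Both reproduce. The 99% cannot be checked on its own terms, because the pilot effect size is not given.

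**Omnibus power at the smallest important difference.** Noncentral F with 3 and 571 degrees of freedom (one covariate), critical F 2.62, and λ = n × SS / SD², where SS is the sum of squared deviations of the four means from their average. The largest gap between any two means is set to the smallest important difference.

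Roland (λ = 144 × SS / 4.71²):

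| Four means | SS | λ | Power |
|---|---|---|---|
| 0, 1, 1, 2 (two middle means at the centre) | 2.00 | 12.98 | 86.8% |
| equally spaced from 0 to 2 | 2.22 | 14.42 | 90.3% |
| 0, 0.5, 1.5, 2 | 2.50 | 16.23 | 93.6% |
| 0, 0, 1, 2 | 2.75 | 17.85 | 95.6% |
| 0, 0, 0, 2 (one versus three) | 3.00 | 19.47 | 97.1% |
| 0, 0, 1.5, 2 | 3.19 | 20.69 | 97.8% |
| 0, 0, 2, 2 (two equal pairs) | 4.00 | 25.96 | 99.5% |

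Power of 99% needs λ = 23.68, that is SS = 23.68 × 4.71² / 144 = 3.65. With a range of 2.0 the largest possible SS is 4.00, so only patterns close to two equal pairs get there. Otherwise the range itself must be larger: 2.70 with the middle means at the centre, 2.56 equally spaced, 2.21 for one versus three.

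Bothersomeness (range 1.5, SD 2.73): 98.3% with the middle means at the centre (λ = 21.74), 99.1% equally spaced, 99.9% for one versus three, and about 100% for two equal pairs (λ = 43.47).

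**Margin behind the word conservative.** Roland pairwise power reaches 80% when 2.0 / (SD × √(2/144)) = 2.61 + 0.842, so SD = 4.92 (4.91 by noncentral t), about 4.4% above 4.71. With SD held at 4.71, power is 80.3% at 133 per arm and 79.9% at 132. Since 133/160 = 83%, loss above about 17% takes it below 80%.

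**The case against.** The methods section is careful: it conditions the 99% on the pilot effect size and says that the pattern of means matters. That stands, and it confines the error to the abstract's wording. The pilot values are not shown, so the 99% in the methods is not disputed.

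Setting the whole four-arm range to one smallest important difference is also a choice of reading. If each hypothesised step were 2.0 points, for example 0, 0, 2, 4, omnibus power would be essentially 100%. The abstract does not say which reading it intends. That limits the point to a conditional one, but it also shows why the sentence needs rewording.

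Three stronger readings are tempting and are not supported:
- A reader might infer that Roland power is only 87% to 90% unless the means form two equal pairs. Those are the two least favourable patterns tried. With the two comparison arms equal and individualised needling ahead of standardised (0, 0, 1, 2), an ordering compatible with the aims, power is 95.6%; one versus three gives 97.1%.
- A reader might infer that the 99% fails on both outcomes. For bothersomeness it is essentially met.
- A reader might infer that the conservatism statement is false. The Statistical analysis section plans covariates beyond baseline that the power calculation leaves out. As an illustration, if they cut residual variance by 5%, pairwise Roland power would be about 86%. The cutoff of 2.61 is also slightly stricter than the exact Tukey value of 2.577. Neither gain is put forward as a quantified margin, and the SDs carry no stated inflation, so the statement is unsupported but not refuted.

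**Conclusion.** The abstract's power sentence is wrong as written, because it moves a figure computed at the pilot effect size onto the smallest important difference. With that difference taken as the largest gap between any two means, Roland omnibus power is 86.8% to 97.8% in the patterns tried other than two equal pairs, and 99.5% for two equal pairs. The chance of missing such a difference is therefore up to about 13%, where 1% is implied. There is no material shortfall for bothersomeness. The figures rest on the plan's own SDs and on 144 analysed per arm.

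The conservatism statement is a secondary matter: an assurance without a stated margin, on an outcome where pairwise power has little to spare. The sample size, the tests and the pairwise power figures are not in question.

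**What to change.** In the abstract, state that 99% is the omnibus power at the pilot effect size; that for a 2.0-point range on Roland it is about 87% to 99%, depending on how the four means are spread; and that pairwise power at the smallest important difference is 84% for Roland and 98% for bothersomeness. Reporting the pilot effect size or the four assumed means would let readers check the 99%.

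In the closing summary of the sample size section, qualify the conservatism sentence: under the baseline-adjusted calculation, pairwise Roland power falls below 80% if the SD exceeds about 4.9 or if fewer than about 133 per arm are analysed, although further covariates may add some precision.

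The cost is a few reworded sentences with less favourable figures. Enrolment and analysis are unchanged.

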**Conclusion:**

Results of this trial will help clarify the value of acupuncture needling as a treatment for chronic low back pain.

**Trial registration:**

Clinical Trials.gov NCT00065585.

## Background

Back pain is one of the most important health problems in developed countries. More than 50% of adults are bothered by back pain each year [1] and 70% to 80% of adults are afflicted by it at some time in their lives [2]. Back symptoms are the leading cause of visits to orthopedic surgeons and neurosurgeons and the second leading symptomatic reason for visits to all physicians [3]. Back pain is the most costly ailment of working-age adults [4]. An estimated $25 billion are spent on personal medical care for back pain every year and compensation and lost productivity costs are much higher [5].

Back pain patients are often dissatisfied with conventional medical care [6], especially in comparison to care provided by non-MD's including CAM practitioners [7-10]. Back pain is the leading primary reason for visits to licensed acupuncturists, representing about 1 in 7 visits [11], and acupuncturists consider it to be one of the conditions for which acupuncture is most effective [12].

Despite numerous published randomized trials evaluating acupuncture as a treatment for chronic low back pain, the efficacy and effectiveness of acupuncture for this common problem remains unclear. The 1997 NIH Consensus Development Panel on Acupuncture noted "many of these studies provide equivocal results because of design, sample size, and other factors. The issue is further complicated by inherent difficulties in the use of appropriate controls, such as placebo and sham acupuncture groups" [13]. Other reviews published before the study protocol described in this manuscript was proposed (2002) also noted the poor quality of research in this area and urged that scientifically rigorous studies be conducted [14-16]. This study was designed to avoid the methodological shortcomings that have plagued previous studies, including inadequate acupuncture treatments, very small sample sizes, failure to include long-term outcome measures and high rates of loss to follow-up.

Our primary aims are to answer the following questions:

1) Is acupuncture needling more effective than usual medical care for reducing dysfunction or symptom bothersomeness due to chronic low back pain?

We hypothesize that acupuncture needling (both standardized and individualized) will be more effective than usual medical care.

2) Is acupuncture needling more effective that non-insertive simulated acupuncture for reducing dysfunction or symptom bothersomeness due to chronic low back pain?

We hypothesize that standardized acupuncture needling will be more effective than non-insertive simulated needling.

3) Is individualized acupuncture needling more effective than standardized acupuncture needling for reducing dysfunction or symptom bothersomeness due to chronic low back pain?

We hypothesize that individualized acupuncture needling will be more effective than standardized acupuncture needling.

Our secondary aims are to compare the effects of these four treatments on general health status, patient satisfaction with care, days of restricted activity due to back problems, and costs and utilization of services.

By addressing the methodological shortcomings of previous studies, this trial will clarify the extent to which acupuncture can diminish the effect of chronic low back pain on patient functioning and symptoms. Because chronic back pain is a major public health problem and the top reason patients seek acupuncture treatment, an unambiguous assessment is critical for making informed decisions about the most appropriate role for acupuncture in care for back pain.

## Methods and design

### Overview

Eligible participants at two sites will be randomized equally to one of four treatments: individualized acupuncture point stimulation, standardized acupuncture point stimulation, non-insertive simulated acupuncture point stimulation, or usual care (Figure 1). Participants in all three "acupuncture" arms will receive 10 "treatments" involving stimulation of acupuncture points over a 7-week treatment period (two treatments per week for 3 weeks, weekly treatments for 4 weeks).

**Figure 1 F1:**
[figure not shown]
Study Design. Process of recruitment, randomization to treatment, treatment provision, and outcomes assessment.

The acupuncture provided will be in accordance with the principles of Traditional Chinese Medicine (TCM) in terms of point selection and needling details. Although many styles of acupuncture are used in the U.S., we selected TCM because it appears to be the most commonly practiced [11,17] is the basis of the national certification exam for non-physician acupuncturists, and is the foundation of non-physician acupuncturist training in the states in which this trial is being conducted. The treatments will be provided by licensed acupuncturists, the group that provides the vast majority of acupuncture treatments in the United States.

In addition to the assigned treatments, all participants will receive a high-quality book about self-management of back pain and will retain access to the health care services to which they are entitled by their insurance coverage.

Participants will be followed for a one-year period following randomization and primary and secondary outcomes will be assessed by telephone interviewers masked to treatment assignment after 8, 26, and 52 weeks. The primary outcome will be dysfunction due to back pain and bothersomeness of back pain. Secondary outcomes will include general health status, satisfaction with back care, days of restricted activity, and use and costs of back-related health care for the year following randomization.

Bias will be minimized by a clinical protocol designed to offer maximum possible masking in a study of a physical procedure such as acupuncture. Although full double masking is not possible, this design permits masking of the assessor of outcomes and substantial masking of participants and the acupuncturist prescribing a treatment. Participants in the three "acupuncture" groups will know only that they will receive one of several methods of stimulating acupoints.

We will perform an intention-to-treat analysis of the data, i.e., the analysis will be by randomized assignment regardless of participation in treatment sessions. This trial was preceded by a pilot trial to assess the feasibility of a full-scale trial. The pilot study demonstrated the feasibility of carrying out a full-scale trial, provided estimates of recruitment rates, follow-up rates, and sample size requirements, and helped us optimize the clinical procedures [18].

### Study population

This study will focus on patients between 18 and 70 years of age with non-radicular chronic low back pain of mechanical origin (as opposed to infectious, neoplastic, or inflammatory causes). There are many potential causes of low back pain, but in most cases, a precise pathoanatomic diagnosis is unattainable because of the weak associations among symptoms, pathoanatomic changes, and imaging results.

### Inclusion and exclusion criteria

Entry inclusion and exclusion criteria (Table 1) were developed with the goal of maximizing enrollment of appropriate participants while excluding patients who have low back pain of a specific (e.g., spinal stenosis) or complicated (e.g., due to a medical condition) nature, for whom acupuncture is contraindicated (e.g., clotting disorders), or whose medical conditions might make it difficult to receive the treatments (e.g., gross obesity or severe psychiatric conditions). These criteria are intended to exclude patients with medical conditions that might contribute to an increased risk of a severe adverse event, would not allow for fully informed consent, or might lead to misinterpretation of the outcomes (e.g., multiple sclerosis or diabetes whose neurological symptoms might interfere with pain sensation). To maximize the credibility of our simulated acupuncture treatment, we will also exclude people who have had acupuncture treatment in the past because such individuals may be more able to distinguish simulated from actual acupuncture.

**Table 1 T1:** Inclusion and exclusion criteria

Inclusion criteria
Participant plans to continue enrollment in health plan
Between 18 and 70 years of age
At least one primary care visit for back pain within the past 3–12 months
Non-specific, uncomplicated low back pain, i.e., ICD-9 codes:
724.2 Lumbago
724.5 Backache, unspecified
724.8 Other symptoms referable to back
846.0-9 Sprains and strains, sacroiliac
847.2 Sprains and strains, lumbar
847.3 Sprains and strains, sacral
847.9 Sprains and strains, unspecified site of the back
Physician willing to have patients included in the study
Lives within 45 minutes travel time from study clinic

Exclusion criteria
Previous acupuncture for any reason
Low back pain lasting less than 3 months
Mild symptoms (less than 3 on 0 to 10 pain bothersomeness scale)
Specific diseases that could be cause of back pain (metastatic cancer, discitis, herniated disc, vertebral fracture, spinal infection, osteitis condensans ilii, severe or progressive scoliosis, spinal stenosis, spondylolisthesis, ankylosing spondylitis)
Complicated back problems (sciatica, back surgery in prior 3 years)
Other disabling chronic conditions that might confound treatment effects or interpretation of data (e.g., disabling heart or lung disease, diabetic neuropathy, active hepatitis, fibromyalgia, rheumatoid arthritis)
Acupuncture contraindicated or safety not confirmed (clotting disorders, on anticoagulant therapy, heart pacemaker, pregnancy, seizure disorder)
Medico-legal issues (seeking or receiving compensation/litigation for back pain)
Conditions possibly making consenting or treatment difficult (paralysis, inability to lie prone for 45 minutes, major psychoses, dementia, scheduling conflicts, severe vision or hearing problems, lack of transportation, unable to read or speak English)

### Recruitment procedures

Members of Group Health Cooperative in Seattle and Kaiser Permanente Northern California in Oakland whose visits to healthcare providers resulted in diagnoses consistent with non-specific low back pain will be identified from the health plans' automated visit data. Three to 12 months after their visit, potential participants will be mailed a letter that explains the study, describes eligibility requirements, and invites participation. Members interested in participating will sign and return a statement indicating their willingness to be contacted by study staff. An interviewer will then phone the members to answer questions and determine eligibility using a computer program to guide the members through a series of screening questions. If eligible, the study staff guides the patient through the consent process. Once written consent is obtained, an interviewer will contact the potential participant to administer the baseline questionnaire. If still willing to participate, participants will be randomized to one of the four groups. If the participant is randomized to acupuncture, the interviewer will schedule the first two acupuncture appointments.

If necessary, recruitment will be supplemented by advertising the study in the health plan's quarterly magazine, on its website, on bulletin boards in the health plans' medical centers, and by placement on the NIH clinical trials website (clinicaltrials.gov) Finally, if these methods fail to achieve recruitment goals, recruitment letters will be sent to randomly-selected health-plan members without a recent clinic visit for low back pain and who are not known to meet an exclusion criterion.

